### Wound closure

Wound closure will be performed in a standardized fashion, as outlined in detail below. Each recruitment centre will use a wound protector upon entering the peritoneal cavity and at all times attempt to keep contamination to a minimum. Surgical gloves will be changed before commencement of closure and a new instrument set will be used. The wound edges will be washed with povidone iodine (Bethidine©, Mundipharma, Cambridge, UK) following removal of the wound protector.The fascial layer will be closed with slowly absorbable monofilament (that is: 1–0 loop polyester poly(p-dioxanone) or PDS) (Ethicon Inc., Rariton, NJ, USA). The skin will then be closed with skin clips with the wounds appropriately everted. The depth of the subcutaneous tissue will be recorded with a sterile ruler from a pen kit. The length of the laparotomy wound will be recorded and then the randomized dressing will be applied.

If the NPWT fails or if an SSI is recorded, a new NPWT dressing will be applied. For the standard dressing group, a new standard dressing will be applied. In such cases, antibiotics will be empirically started and decisions regarding further surgical intervention will be made at the discretion of the consultant surgeon.

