PICO™ (Smith & Nephew, London, UK) and Prevena™ (KCI, 3M, St Paul, MN, USA) wound management systems are among the most widely used NPWT in surgical practice. Importantly, the PICO trial performed in 2017 illustrated a significant reduction in SSI rate and duration of hospital stay when compared with standard wound dressings^20^. Conversely, the NEPTUNE trial failed to identify any difference in wound infection rates postlaparotomy when comparing Prevena™ to standard dressings in patients undergoing colorectal surgery^21^. Data from the CHIR-Net, PROUD and ROSSINI RCTs demonstrated an incidence rate of 15–25% following gastrointestinal surgery^10–12^, with significant morbidity rates and costs^22^. Furthermore, most trials included short durations of follow-up (median: 7 days)^23^, with no trials comparing different types of NPWT and conflicting results from different devices trialled^21,22^. Additionally, there are limited data available on economic analyses for gastrointestinal surgery indications^23^. Accordingly, the necessity to identify novel interventions to reduce SSI incidence is imperative, yet given the heterogeneity of results, there are no consensus statements or guidelines recommending the routine use of prophylactic NPWT to prevent SSI postlaparotomy.

Thus, the aim of the PROPEL-2 trial is to determine whether NPWT confers a lower rate of SSI following laparotomy. The hypothesis is that patients randomized to NPWT will have a lower incidence of SSI.

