### Negative pressure wound therapy

NPWT dressings use an open cell foam laid on top of the wound. It is then covered with an impermeable adhesive membrane. A sealed tube punctures the membrane to connect the dressing to the in-built pump leading to the creation of a partial vacuum of the wound. Generally, the first dressing applied at the end of the operation is left in place until the wound is ready for sutures to be removed at approximately 7–10 days. The number of replacement NPWT dressings within the first 30 and 90 days will be captured.

The Prevena^TM^ (Kinetic Concepts Inc, San Antonio, TX, USA) Incision Management system is comprised of a suction unit that has a small canister for fluid collection, tubing and a sponge dressing with a non-adherent layer and semipermeable adhesive drape. Prevena^TM^ contains a 0.019% ionic silver solution which has utility in preventing bacterial growth in the dressing. The system is ergonomic as it is supplied with a carrying case to minimize negative implications on patient mobility. When applied and activated, this system maintains a closed environment and removes any potential fluid which may collect at the wound site via the application of negative pressure therapy.

The PICO^TM^ (Nephew Wound Management, London, UK) is a NPWT system that consists of a silicone wound interface dressing that is applied directly onto the wound. The purpose of this interface is to transmit even pressure distribution across the wound bed, while negative pressure is transmitted from the wound filler at −80 mmHg.

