#### Secondary outcome measures

The secondary outcome measures in this trial are to compare the use of standard dressings with NPWT dressings in terms of impact on quality of life (QoL), with the EuroQoL EQ-5D-5L questionnaire and Quality Adjusted Life Year (QALY) profiles^26^, wound healing and scar appearance (using the POSAS questionnaire and the photograph taken at each follow-up visit)^25^, postoperative complications (obtained from the patient chart for this study) and economic settings (using the validated CoPaQ questionnaire for patients^27^). Incidence rates of skin blistering, allergic reactions to dressings and device/dressing malfunction were also evaluated. *Figure 1* outlines the CONSORT diagram for the PROPEL-2 trial.

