### Power calculation

For planning purposes, it is assumed 15% of participants randomized to standard dressings will develop an SSI and the rate among patients receiving prophylactic, single-use NPWT will be 10% (that is a relative risk reduction of 33%, absolute risk reduction 5%). To achieve 90% power at the 5% significance level, a minimum of 1006 patients will be required in each arm. To allow for losses to follow-up and withdrawals, 10% will be added to each arm. Therefore, the total projected sample size for PROPEL-2 is 2013 patients. This power calculation for PROPEL-2 did not estimate or account for subgroups, including elective and emergency laparotomy wounds or surgical procedures performed.

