### Statistical analysis

Standard statistical summaries and graphical plots will be presented for the primary outcome measure and all secondary outcome measures. Baseline data will be summarized to check comparability between treatment arms.

The main analysis will investigate differences in the primary outcome measure: the proportion of patients with any SSI at 30 and 90 days postlaparotomy. While clustering effects are not expected to be important for this study, in reality the data will be hierarchical, with patients naturally clustered into groups by recruiting centre. This will be accounted for by generalizing the conventional linear (fixed-effects) regression approach to a mixed-effects logistic regression analysis. This model will be used to assess differences in SSI rates between the study intervention groups, with results presented as odds ratios with associated 95% confidence intervals. The mixed-effects model will include a random effect to account for any heterogeneity in response due to the recruitment centre and fixed effects to adjust for emergency *versus* elective procedure and surgical specialty. An identically structured and formulated mixed-effects linear regression model will be used to assess the effects of the interventions on secondary outcomes and EQ-5D and WoundQoL (at both 3 and 6 months) that, for the purposes of analysis, will be assumed to be approximately normally distributed. Other dichotomous outcome variables, such as complications related to the trial interventions, will be analysed in the same manner as the primary outcome. Temporal patterns of any complications will be presented graphically and if appropriate a time-to-event analysis (Kaplan–Meier survival analysis) will be used to assess the overall risk and risk within individual classes of complications.

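### Read literally, the re-dressing rule starts antibiotics for NPWT failure without infection, and it states no trigger for the standard dressing arm

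*Protocol article*

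**What the plan says.** Three consecutive sentences of the protocol article (Methods, Wound closure) set the rule:

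- NPWT arm: "If the NPWT fails or if an SSI is recorded, a new NPWT dressing will be applied".
- Control arm: "For the standard dressing group, a new standard dressing will be applied". This sentence names no triggering event.
- Antibiotics: "In such cases, antibiotics will be empirically started". The same sentence goes on to leave any further operation to the consultant.

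Other sections bear on how the rule works:

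- Secondary outcome measures treats malfunction as an outcome in its own right: "Incidence rates of skin blistering, allergic reactions to dressings and device/dressing malfunction were also evaluated".
- Negative pressure wound therapy expects replacements: "The number of replacement NPWT dressings within the first 30 and 90 days will be captured".
- Statistical analysis defines the primary comparison as "the proportion of patients with any SSI at 30 and 90 days postlaparotomy", by intention to treat.
- The Introduction states the hypothesis for the dressing alone: "The hypothesis is that patients randomized to NPWT will have a lower incidence of SSI". The Power calculation does the same, assuming 15% SSI in controls and that "the rate among patients receiving prophylactic, single-use NPWT will be 10" per cent.

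**The concern.** Antibiotics given before any infection act on the outcome the trial measures. If they follow from dressing failure, and failure is commoner with one dressing, the arms differ in more than the dressing. The intention-to-treat analysis does not remove this, because the co-treatment arises from the allocated arm. Part of a lower SSI rate could then be an antibiotic effect credited to NPWT.

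The opposite error is also possible. SSI is diagnosed by the treating team, and the Discussion accepts that the trial is open label. A team that has started antibiotics may be readier to record an infection.

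Apart from bias, the literal rule exposes uninfected patients to antibiotics, and centres that read it differently will treat the same event differently.

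**Working it through.** **Reading the text**

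1. The NPWT sentence joins device failure and a recorded SSI with an *or*, so each is a trigger on its own.
2. The antibiotic sentence refers back to such cases without limiting them to SSI. No other section narrows it.
3. Malfunction is listed as an outcome separate from SSI, so failure without infection is foreseen.
4. The control sentence must borrow its trigger from the sentence before. If it borrows SSI only, antibiotics before any SSI occur in the NPWT arm alone. If it borrows both triggers, they occur in both arms, and the imbalance is the difference in failure rates.
5. The NPWT device has a sealed membrane, a tube and a pump. The standard dressing uses no negative pressure. An excess of failures with NPWT is therefore likely, but the article does not quantify it.

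**The plan's own figure**

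Unpooled normal formula, two-sided 5%, 90% power:

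n = (1.960 + 1.282)² × (0.15 × 0.85 + 0.10 × 0.90) / 0.05² = 914.1, rounded up to 915 per arm.

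915 × 1.1 = 1006.5 per arm, and 2 × 1006.5 = 2013, which is the stated total. Both 1006 and 915 per arm are used below.

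**Illustrative size**

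From the article: 15% control SSI rate, 5-point planned difference, 1006 per arm. Assumed, because the article gives neither:

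- d, the excess share of NPWT patients with failure before any SSI: 2 to 20%.
- e, the relative reduction in later SSI from the antibiotics: 25 to 50%.

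With no true dressing effect:

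- NPWT rate p = 0.15 × (1 − d × e)
- Chance of a significant result favouring NPWT = P(Z > 1.96 − (0.15 − p)/SE), with SE = √{[0.15 × 0.85 + p(1 − p)]/n}

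Example, d = 0.10 and e = 0.50: p = 0.15 × 0.95 = 0.1425, so the difference is 0.75 points. SE = √{(0.1275 + 0.1222)/1006} = 0.01575. The chance is P(Z > 1.96 − 0.476) = 6.9%.

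| d | e | NPWT rate | False difference (points) | Share of planned 5 | Chance of false win, n = 1006 |
|---|---|---|---|---|---|
| 2% | 25% | 14.93% | 0.08 | 1.5% | 2.8% |
| 2% | 50% | 14.85% | 0.15 | 3% | 3.1% |
| 5% | 25% | 14.81% | 0.19 | 4% | 3.3% |
| 10% | 25% | 14.63% | 0.38 | 7.5% | 4.2% |
| 10% | 50% | 14.25% | 0.75 | 15% | 6.9% |
| 20% | 50% | 13.50% | 1.50 | 30% | 15.9% |

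The nominal chance is 2.5%. At 915 per arm the last four rows give 3.2%, 4.1%, 6.6% and 14.9%. The odds ratio runs from 0.985 (5%, 25%) to 0.884 (20%, 50%). Uninfected patients given antibiotics: d × 1006 = 50 at d = 5% and 201 at d = 20%.

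**Why such starts should not be counted as SSI**

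If the planned 10% NPWT rate is true, recoding a share d of uninfected patients as SSI gives 0.10 + 0.90 × d. This reaches the control rate of 15% at d = 0.05/0.90 = 5.6%. At d = 10% it is 19%, and at 20% it is 28%. A wholly real benefit would vanish or reverse.

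**The case against.** The strongest reply is that the sentence means SSI only. Its second half concerns further surgery, which fits an infected wound better than a lost seal, and empirical treatment suggests suspected infection. Failure of the NPWT could also mean clinical failure, since the article uses a different term when it lists malfunction as an outcome. This makes an SSI-only intent plausible. It does not change what is written: the discretion in that sentence covers surgery, while antibiotics are directed.

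A second reply is that the control sentence is elliptical and borrows the preceding condition, so the rule is the same in both arms. That is possible. A reader might infer that the plan reserves pre-infection antibiotics for NPWT patients. The documents do not establish this, because it requires that the antibiotic sentence covers malfunction and also that controls borrow only the SSI half.

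A third reply concerns size, and it largely stands. Both inputs are assumed. The dressing usually stays on for about 7 to 10 days while SSI is counted to 30 and 90 days, so a constant 50% reduction is generous. The diagnostic error described above could act in the other direction.

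Finally, the article is a condensed account and the full protocol may carry a clearer rule. The point here is a rule the article does state, and states too broadly, so it is not a complaint about missing detail.

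**Conclusion.** The point holds as a defect in a stated treatment rule. Followed as written, it gives antibiotics to patients with a dressing failure and no infection, leaves the control trigger unstated, and lets a co-treatment act on the primary outcome, probably more often in the NPWT arm.

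The size of any bias is unknown. It is negligible at a 2% excess of failures. It reaches 1.5 points, 30% of the planned difference, only with a 20% excess and a halving of later SSI. A reader might infer that the primary comparison is confounded or that the type I error is inflated by a known amount. The documents support neither: they give no failure rate and no antibiotic effect, the direction is not certain, and the authors may have meant SSI only. The rule should be corrected because the correction is cheap and centres need a single reading.

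**What to change.** Replace the rule under Wound closure with two rules, worded identically for both arms:

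1. Dressing or device failure without suspected or recorded SSI: replace with the allocated dressing type, and start no antibiotics because of the failure.
2. Suspected or recorded SSI, by the Centre for Disease Control criteria the article already names: replace with the allocated dressing type and start empirical antibiotics.

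Enrolment began in June 2023, so for patients already treated report by arm the number who started antibiotics after dressing failure and before any SSI. Do not recode those starts as SSI, for the reason shown in the working.

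The cost is two or three sentences, a note to centres and one descriptive table. The sample size, visits and primary analysis do not change.

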### Patient trial identification number assignment

The patient trial number will then be used to enter patient data on a secure, encrypted, web-based system, REDCap (ProjectREDCap, Nashville, TN, USA). Basic information regarding age and eligibility checks will be entered.

### Statistical analysis

Standard statistical summaries and graphical plots will be presented for the primary outcome measure and all secondary outcome measures. Baseline data will be summarized to check comparability between treatment arms.

The main analysis will investigate differences in the primary outcome measure: the proportion of patients with any SSI at 30 and 90 days postlaparotomy. While clustering effects are not expected to be important for this study, in reality the data will be hierarchical, with patients naturally clustered into groups by recruiting centre. This will be accounted for by generalizing the conventional linear (fixed-effects) regression approach to a mixed-effects logistic regression analysis. This model will be used to assess differences in SSI rates between the study intervention groups, with results presented as odds ratios with associated 95% confidence intervals. The mixed-effects model will include a random effect to account for any heterogeneity in response due to the recruitment centre and fixed effects to adjust for emergency *versus* elective procedure and surgical specialty. An identically structured and formulated mixed-effects linear regression model will be used to assess the effects of the interventions on secondary outcomes and EQ-5D and WoundQoL (at both 3 and 6 months) that, for the purposes of analysis, will be assumed to be approximately normally distributed. Other dichotomous outcome variables, such as complications related to the trial interventions, will be analysed in the same manner as the primary outcome. Temporal patterns of any complications will be presented graphically and if appropriate a time-to-event analysis (Kaplan–Meier survival analysis) will be used to assess the overall risk and risk within individual classes of complications.

The primary focus will be to compare the two treatment groups on an intention-to-treat (ITT) basis, and this will be reflected in the analysis which will be reported together with appropriate diagnostic plots that check the underlying model assumptions. In addition to the ITT analyses, per-protocol (as treated) analyses will also be undertaken and reported in parallel to, but subsidiary to, the main analyses. Where possible the reasons for missing data will be determined. Although missing data is not expected to be a problem for this study, the nature and pattern of the ‘missingness’ will be considered—including in particular, whether data can be treated as missing at random (MAR). If judged appropriate, missing data will be imputed, using multiple imputation. The resulting imputed data sets will be analysed and reported, together with appropriate sensitivity analyses. Any imputation methods used for scores and other derived variables will be reviewed by the Data Monitoring Committee (DMC). Reasons for ineligibility, non-compliance, withdrawal or other protocol violations will be stated if available and any patterns summarized. More formal analysis, for example using logistic regression with ‘protocol violation’ as a response, may also be appropriate and aid interpretation.

All reported tests will be two-sided and considered to provide evidence for a significant difference if *P* values are less than 0.05 (5% significance level). A detailed statistical analysis plan (SAP) will be agreed with the DMC before commencement of the study. Any subsequent amendments to this initial SAP will be clearly stated and justified in the final report. Interim analyses of efficacy outcomes are not planned and will be performed only where requested by the DMC. Data will be analysed using Statistical Package for Social Sciences™ (SPSS™) version 26.0 (International Business Machines Corporation, Armonk, NY, USA).

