## Introduction

In recent decades, contemporary surgical practice has focused upon optimizing perioperative factors to enhance clinical outcomes for patients indicated to undergo surgery^1^. Surgical site complications remain a significant burden on surgical practice^2^, having negative implications on patient health, quality of life metrics and the cost effectiveness of the provision of surgical care. Surgical site infections (SSIs) are defined as incision or deep tissue infections at the operation site occurring up to 30 days after surgery^3^. SSIs constitute negative implications for surgical patients' postoperative recovery, through prolonging inpatient hospital stays, necessitating additional antimicrobial treatment, and in severe cases, leading to reintervention^4,5^.

Recent efforts have focused on identifying novel strategies to reduce SSIs^6,7^, yet the average incidence remains consistent in 0.5–3.0% of all surgical patients^8^ and 11.0% of general surgery patients^9^. Randomized clinical trial (RCT) data illustrates that SSIs have an incidence of 15–25% following colorectal and emergency abdominal surgery^10–12^.

The hypothesis supporting the use of suction-based drainage of infected wounds was first described by Soviet scientists in the mid-1980s for complex, contaminated wounds, with these preliminary results supporting their use in such cases^13,14^. The prophylactic application of negative pressure wound therapy (NPWT) devices was subsequently proposed as a novel strategy to combat chronic wound infections, following the publication of promising results from an animal study in 1997^15^. Thereafter, the application of NPWT for wound complications came into vogue^16,17^: in 2016, Hyldig *et al*. performed a meta-analysis of 10 RCTs which illustrated a relative risk reduction of 50% for wound infection and seroma formation relative to standard dressings^18^, albeit results were limited due to heterogeneity between the studies included. Sahebally *et al*. then performed a meta-analysis of 1266 patients which demonstrated a 75% relative reduction in SSI for patients who had NPWT applied to their closed abdominal surgery wounds^19^.

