### Study objectives

The primary objective for the trial is to quantify and analyse differences in the rates of midline wound SSI in the 30 and 90 days following laparotomy between NPWT and standard dressings. The diagnosis of SSI will be made using Centre for Disease Control criteria.

The secondary objectives are to analyse health-related quality of life in the 6 months following laparotomy and to assess the quality of wound healing and cost effectiveness. Another objective is to analyse the further interventions related to laparotomy and the risk of developing SSI related to the subcutaneous adiposity and lean muscle mass using preoperative computed tomography (CT). In a nested Study Within A Trial (SWAT), another objective is to determine the impact of digital prompts (for example using e-mail) to research team members on site trial recruitment rates.

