### Outcome measures

#### Primary outcome measure

The primary outcome measure is the incidence of any SSI. The treating clinical team who will make the diagnosis will not be members of the research team. For the purposes of the trial, any wound infection requiring ongoing medical intervention/which has led to reoperation at or after the 30 and 90 day review will be considered a deep SSI.

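### Any SSI at 30 days and at 90 days are both primary, unranked and each judged at P<0.05, while the sample size covers one undated comparison; the success rule is undefined

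*Protocol article*

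**What the plan says.** - **Study objectives.** The primary objective concerns "differences in the rates of midline wound SSI in the 30 and 90 days following laparotomy between NPWT and standard dressings". Neither time point is placed first.
- **Primary outcome measure.** "The primary outcome measure is the incidence of any SSI", with no time point attached.
- **Statistical analysis.** The main analysis compares "the proportion of patients with any SSI at 30 and 90 days postlaparotomy". On the threshold: "All reported tests will be two-sided and considered to provide evidence for a significant difference" when P is below 0.05. This covers every test, with no exception or adjustment for the two primary time points.
- **Power calculation.** SSI rates of 15% (standard dressing) and 10% (NPWT) are assumed, with no day given. "To achieve 90% power at the 5% significance level, a minimum of 1006 patients will be required in each arm". Ten per cent is added for losses, and the total is 2013.

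The article contains no hierarchy, no split of the 5%, no rule that both days must be significant, and no lead time point.

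**The concern.** Two primary results, each judged at 5%, can be combined into a trial conclusion in more than one way, and the article does not choose. If either result suffices, the chance of a false positive exceeds the 5% on which the sample size was built. If both are required, the chance of success under the planning assumptions can be well below 90%. If one is significant and the other is not, the reader cannot tell from the plan whether NPWT has been shown to work.

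The gap matters more here than in a blinded trial. The Discussion accepts that the study is open label, and the treating team makes the diagnosis. Freedom to choose the lead time point after seeing the results would add to that acknowledged risk of bias.

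**Working it through.** **1. The plan's own figure.** Inputs from Power calculation: 15% and 10%, two-sided 5%, 90% power, 10% added. With unpooled variance:

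n per arm = [0.15×0.85 + 0.10×0.90] × (1.960 + 1.282)² / 0.05² = 0.2175 × 10.507 / 0.0025 = 914.1, so 915.

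915 × 2 × 1.10 = 2013, which is the stated total. The trial is thus sized for a single test at two-sided 5%. After 10% loss, 2013/2 × 0.9 ≈ 906 per arm are analysed. (The article calls 1006 per arm the number before the 10% is added, whereas 915 × 1.10 = 1006.5. That is a separate point; 906 is used below, with 1006 as a check.)

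**2. Either day counts as success.** SSIs by day 30 are contained in the 90-day count, so the tests are correlated. For nested cumulative proportions

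r = √[p30(1 − p90) / (p90(1 − p30))].

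The type I error is the probability under a bivariate normal that at least one |Z| exceeds 1.960. The share of 90-day SSIs that occur by day 30 is not in the article, so 50% to 90% is assumed. With p90 = 12.5%, the mean of the two planning rates:

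| Share by day 30 | r | Type I error |
|---|---|---|
| 90% | 0.942 | 6.6% |
| 80% | 0.882 | 7.2% |
| 70% | 0.819 | 7.7% |
| 50% | 0.683 | 8.4% |

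Using p90 = 15% moves no entry by more than 0.03 percentage points. Independent tests would give 1 − 0.95² = 9.75%, an upper limit that the overlap keeps out of reach.

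**3. Both days must be significant.** The type I error is then at most 5%. Power of one test is

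Φ[(d − 1.960·se0)/se1], with se0 pooled and se1 unpooled.

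Suppose 15% and 10% are the 90-day rates and the relative effect is the same at day 30. With 906 per arm, the 90-day test has se0 = 0.01554 and se1 = 0.01549, so power is Φ(1.26) = 89.6%. At day 30, with 80% of SSIs by then, the rates are 12% and 8%: se0 = 0.01410, se1 = 0.01406, and power is Φ(0.88) = 81%. Joint power uses the bivariate normal with r from step 2.

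| Share by day 30 | Day-30 rates | Day-30 power | Joint power |
|---|---|---|---|
| 90% | 13.5% vs 9% | 86% | 85% |
| 80% | 12% vs 8% | 81% | 80% |
| 70% | 10.5% vs 7% | 75% | 74% |
| 50% | 7.5% vs 5% | 59% | 58% |

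With 1006 analysed per arm, joint power runs from 63% to 88%, still below 90%.

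If 15% and 10% are instead 30-day rates, the 90-day rates are higher and that test has more power than 89.6%. For example, 15%/0.9 = 16.7% against 10%/0.9 = 11.1% gives 93%. Joint power is then about 89%, close to that of the single test. The power loss is therefore material only if the planning rates are 90-day rates, and the article does not say which they are.

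**4. Split result.** No sentence in Study objectives, Primary outcome measure or Statistical analysis says what follows from significance at one day only.

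**The case against.** **The analysis plan may settle this.** The article defers detail to a plan agreed with the data monitoring committee, and multiplicity is often handled there. This stands in part: that plan is not available and may rank the two days. But the article itself fixes two primary time points and one unadjusted threshold for every test, and leaves its planning rates undated. A later ranking would have to amend those statements.

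**The 5% is not shown to be broken.** A reader might infer that the type I error is inflated as a matter of fact. The article does not say that success at either day suffices, and under a both-days rule 5% is held. What is established is that no rule is given. The 6.6% to 8.4% applies to one reading and rests on an assumed share of SSIs by day 30.

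**Supporting points that do not carry weight.**
- A reader might infer that a 90-day primary contradicts the trial's own definition, because the Introduction describes SSI as "defined as incision or deep tissue infections at the operation site occurring up to 30 days after surgery". That is a cited background sentence. Study objectives sets both windows and takes the diagnosis from Centre for Disease Control criteria.
- The open-ended sentence under Primary outcome measure, "at or after the 30 and 90 day review will be considered a deep SSI", decides when an infection is called deep. The primary outcome is any SSI, so depth does not affect the error rate.
- Only the 1-month photograph is said to help diagnose infection. It only assists the treating team, and a 3-month visit is scheduled, so this does not show that day 30 was meant to lead.

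**Conclusion.** The point holds as an undefined success rule for the primary outcome. It needs to be settled before results by arm are seen, because the meaning of the primary result depends on it.

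Its size depends on the reading:
- Either day suffices: type I error about 6.6% to 8.4%, a moderate excess over 5% and well below 10%.
- Both days required: 5% held; joint power about 58% to 85% if the planning rates are 90-day rates, and close to that of the single test if they are 30-day rates.
- Split result: no verdict.

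The figures assume that 50% to 90% of 90-day SSIs occur by day 30, the same relative effect at both days, and 906 patients analysed per arm. Only the last of these can be derived from the article. A reader might also infer that day 30 is the right primary, or that choosing it costs no power. The article supports neither: it favours no day, and if its rates are 90-day rates, a day-30 primary has about 81% power when 80% of SSIs occur by then.

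**What to change.** Before any comparison by arm (enrolment began in June 2023):

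1. Name one time point, 30 or 90 days at the sponsor's choice, as the sole primary outcome. Word it identically in Study objectives, Primary outcome measure and Statistical analysis, and test it at two-sided 5%.
2. Make any SSI at the other time point the first secondary outcome, tested at two-sided 5% only if the primary is significant. This fixed order holds 5% across the pair and defines the verdict on a split result.
3. State in Power calculation which day the 15% and 10% describe. If it is not the chosen primary day, give the rates expected on that day and restate the power; the 12% against 8% case above, at about 81%, is an example.

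The cost is protocol and analysis-plan wording and a registry update; no new data are needed. One time point becomes secondary, and the restated power may be less favourable than 90%.

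Keeping two primaries with 2.5% each would also hold 5%, but at greater cost. For 15% against 10%, the calculation in step 1 with 2.5% in place of 5% gives 1080 per arm, or 1080 × 2 × 1.10 = 2376 patients in place of 2013.
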